
#### Aim 3. Genetic relation of ARFID to other eating disorders

Greater detail on Aim 3 analyses can be found in the *Supplement*.*Disorder-specific GWAS*. We will conduct disorder-specific GWAS for ARFID (and AN, BN, and BED as part of other projects) combining ARFID-GEN with EDGI and existing PGC-ED data using imputed variant dosages and an additive model. We anticipate aggregate sample sizes for the PGC-ED by ~ 2025 (when our collection would be complete) of: (Projected: ARFID = 3,000, AN = 50,000, BN = 20,000, BED = 20,000, ARFID-GEN controls [sourced from existing data repositories] = 42,439, PGC-ED controls = 543,967). GWAS meta-analysis will be conducted with ARFID-GEN and any other ARFID samples that may be introduced to the PGC-ED by time of analysis.*Combined eating disorder GWAS*. Combining ARFID-GEN with PGC-ED GWAS of AN, BN, and BED (which will be available by the time our data are analysis-ready), conduct GWAS meta-analysis of all EDs and of component behaviors that cross-cut disorders (e.g., binge eating, restriction), increasing power to identify genetic risk factors that are common across the four disorders.*Genetic correlations.* Common variant-based genetic correlations (SNP-*r*_g_) measure the extent to which two traits or disorders share common genetic variation. We will calculate SNP-*r*_g_ for ARFID, and selected traits using GWAS summary statistics via an analytical extension of LDSC [36, 37], as well as explore genome-based restricted maximum likelihood (GREML), which was recently shown to have higher accuracy than LDSC [45]. Risk factors classically considered as environmental, such as exercise for AN, are now known to be complex traits underpinned by genetic and non-genetic factors. Large community cohorts like United Kingdom (UK) Biobank, generate GWAS summary statistics for a plethora of phenotypes (e.g., diet, medication, blood metabolites). It is very fast to estimate r_g_ from GWAS summary statistics, and this screening process has the potential to identify unknown associations which will guide the hypotheses of down-stream analyses.*Generalized summary data-based Mendelian randomization (GSMR)*. Guided by the r_g_ estimated above and our hypotheses, we will perform bidirectional MR analyses to investigate causal relationships between correlated traits and ARFID. For example, it is reasonable to test hypotheses of causality using anxiety as an exposure for ARFID. Significant MR results must be reviewed with caution with respect to strong conclusions about causality as unmeasured confounders may exist. Nonetheless, these analyses are potentially exceptionally informative. MR analyses take SNPs that are genome-wide significant for one trait (the exposure) and test the correlation in effect sizes in a second trait (the outcome). Under pleiotropy, there is an expectation that the mean effect size in the outcome trait is different from zero, but under causality a directional relationship in effect sizes is expected. Different versions of MR analysis are highly related; at the time of analysis, we will implement best practices for MR.*Multi-trait-based conditional and joint analysis*. Results from a) and b) will inform these analyses. For example, we expect to detect genetic correlations of BMI with EDs, and MR analyses will aid interpretation of correlation by causality. We will conduct conditional GWAS analyses to determine if the detected SNP associations for EDs can be explained through their relationship with correlated traits. We will perform a multi-trait-based conditional and joint analysis (GCTA-mtCOJO) [16] using an extension of GCTA [46]. This method uses summary-level data to perform conditional analyses. Based on our previous work, we expect to condition the results of our ARFID GWAS on the best available GWAS results for relevant traits including intelligence quotient (IQ), education years, type 2 diabetes, high density lipid cholesterol, BMI, schizophrenia (SCZ), MDD, ASD, OCD, and neuroticism. Comparing these results to those generated from unconditional GWAS results (i.e., from a above) provides insights into the forces shaping the shared genetic relationships between disorders.*Disorder-specific SNP associations*. A key question in ED research is to understand the differences as well as the similarities among the EDs. This question is very similar to the one posed by PGC colleagues interested in understanding the similarity/differences between SCZ and bipolar disorder (BIP) [47]. Guided by their analyses, we will conduct case vs. case (e.g., ARFID-AN) GWAS. This approach is powerful if case samples can be grouped (e.g., if genotyped together so that technical confounding factors are not present), as sampling errors associated with control allele frequency estimates are avoided.*Multi-polygenic score (MPS)*. To gain insight into factors underlying ED heterogeneity, we will use the largest available GWAS summary statistics for psychiatric and somatic disorders/traits and combine derived PRS into MPS to predict target outcomes (ARFID, AN, BN, or BED diagnosis), and then more granular phenotypes (e.g., age of onset, severity, low weight). Combining ARFID-GEN with EDGI and existing AN, BN, and BED cohorts in the PGC-ED samples should yield a sample size of ~ 95,000 ED cases and > 500,000 controls. We will increase power by using MPS to combine the predictive power of several PRS in one regression model. Training data will combine the best available GWAS summary statistics on psychiatric, metabolic, BMI, anthropometric, personality, physical activity, and educational phenotypes. These PRS will be used as genetic predictors in models of ARFID, AN, BN, BED, and more granular phenotypes. This approach is ideal for our overarching intentions of predicting outcomes rather than discovering their etiology (i.e., using, not finding genes). MPS is valuable when trait prediction is a priority.*GSEM.* We will use lifetime ARFID, AN, BN, and BED GWAS summary statistics. We will employ GSEM [18] to identify genetic factors for ARFID and associated EDs. GSEM is a multivariate method for analyzing the joint genetic architecture of complex traits. By modeling covariance structure, GSEM synthesizes genetic correlations and SNP heritabilities inferred from GWAS summary statistics of individual traits from samples with varying and unknown degrees of overlap. GSEM analyses will include several steps, including a factor analysis of correlated traits, estimating SNP effects and computation of factor-level PRS.

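### The Mendelian randomisation section separates pleiotropy from causality by a contrast that does not discriminate, because shared genetic effects also give a directional relationship

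*Protocol article*

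**What the plan says.** The protocol article, Planned data analysis, Aim 3, GSMR paragraph, states the purpose and the choice of traits: "Guided by the r_g_ estimated above and our hypotheses, we will perform bidirectional MR analyses to investigate causal relationships between correlated traits and ARFID". It describes the procedure in two steps: "MR analyses take SNPs that are genome-wide significant for one trait (the exposure"), and these SNPs are used to "test the correlation in effect sizes in a second trait (the outcome"). It then gives its guide to interpretation: "Under pleiotropy, there is an expectation that the mean effect size in the outcome trait is different from zero, but under causality a directional relationship" between the two sets of SNP effects. Anxiety as an exposure for ARFID is its worked example.

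The paragraph also holds two safeguards: "Significant MR results must be reviewed with caution with respect to strong conclusions about causality as unmeasured confounders may exist", and "at the time of analysis, we will implement best practices for MR". The next paragraph, on multi-trait conditional analysis (mtCOJO), says of BMI and eating disorders that "MR analyses will aid interpretation of correlation by causality". Aim 4 applies the same approaches to psychiatric, metabolic and neurodevelopmental traits.

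**The concern.** The question asked is causal, but the quantity tested is a correlation of SNP effects, so the null actually tested is no such correlation. A non-zero genetic correlation without any causal path breaks that null. Exposures are picked partly because they are genetically correlated with ARFID, so the weakness falls on the very traits that will be tested. Aim 3 itself hypothesises that ARFID shares a core set of genetic factors with other eating disorders, which is a non-causal source of correlated effects.

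A reader who applied the printed contrast would take a directional relationship as a mark of causality. Genetic overlap alone could then be reported as, say, an effect of anxiety on ARFID, and the same reading could colour the interpretation of the mtCOJO results.

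**Working it through.** The article gives no power, alpha or error rate for GSMR, so there is no figure to reproduce.

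**Step 1: algebra, with no assumed inputs.** Let b_x and b_y be a SNP's effects on exposure and outcome.

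- Shared effects, no causal path: E[b_y | b_x] = r_g × sqrt(h2y/h2x) × b_x. This is a directional relationship without causation.
- Causal effect of slope b: E[b_y | b_x] = b × b_x. With alleles aligned so that b_x > 0, the mean outcome effect is b × mean(b_x), which is not zero.

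Both states therefore show both signatures.

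**Step 2: size.** From the article: 3,000 cases, 42,439 ARFID-GEN controls, and a genome-wide threshold of 5 × 10^-8 (|z| > 5.45). Effective N = 4/(1/3,000 + 1/42,439) = 11,208. Assumed, because the documents do not give them: exposure SNP-h2 0.10, ARFID SNP-h2 0.05-0.20 (on the scale matching effective N), M = 6,000 causal variants, exposure GWAS of 150,000 or 500,000, two-sided alpha 0.05.

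Let λ = N × 0.10/6,000 and t = 5.45/sqrt(1+λ), with φ and Q the normal density and upper tail. The instrument count is n = 6,000 × 2Q(t). The mean squared z of selected SNPs is E = (1+λ)(1 + tφ(t)/Q(t)). With s = λ/(1+λ), the share of exposure heritability that the instruments carry is f = n(s²E + s)/(N × 0.10).

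| Exposure N | λ | t | n | E | f |
|---|---|---|---|---|---|
| 150,000 | 2.50 | 2.913 | 21 | 36.2 | 0.027 |
| 500,000 | 8.33 | 1.784 | 447 | 45.7 | 0.333 |

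The expected GSMR z with no causal effect is about r_g × sqrt(11,208 × h2y × f), and the rejection rate is about Φ(z − 1.96):

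| Instruments | r_g | z (h2y 0.05 to 0.20) | Rejection |
|---|---|---|---|
| about 21 | 0.2 | 0.78 to 1.57 | 12% to 35% |
| about 21 | 0.3 | 1.18 to 2.35 | 22% to 65% |
| about 450 | 0.2 | 2.73 to 5.47 | 78% to 100% |
| about 450 | 0.3 | 4.10 to 8.20 | 98% to 100% |

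Simulations with bivariate-normal SNP effects and the same inputs agree: 74-100% over r_g 0.2-0.3 with about 450 instruments, and 10-65% with about 21. At r_g = 0 the slope test rejects in 6-10%.

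**Step 3: do the signatures differ between the two states?** A second simulation used ARFID SNP-h2 0.15 on the liability scale, prevalence 3% (the article gives 2-5%), an outlier filter at p < 0.01, and r_g 0.3 or a causal effect of equal slope:

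| Instruments | Slope test: shared / causal | Aligned mean effect: shared / causal |
|---|---|---|
| about 26 | 81% / 89% | 77% / 92% |
| about 156 | 99% / 100% | >99% / 100% |
| about 1,100 | 100% / 100% | 100% / 100% |

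Neither signature separates the states. The MR-Egger intercept flagged 4-8% of the shared-effect data sets, about its nominal 5%, so that common sensitivity check does not help.

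**Step 4: sensitivity.** With the liability-scale h2 and f set directly, rejection at r_g 0.3 runs from 13% (h2 0.05, f 0.01) through 90% (h2 0.15, f 0.05) to 100% (h2 0.15, f 0.20). A Bonferroni correction for an assumed 20 traits lowers the 90% to 58%.

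**The case against.** The strongest reply is that the sentence is background. A reader might infer from it that correlated traits will usually be declared causal, but the documents do not support that. The article states no null, alpha or decision rule for GSMR, makes MR conditional (if indicated, under Specific aims, Aim 3), asks for caution, and defers method choice to best practice and detail to a Supplement that is not shown. The word usually also fails for weak exposures, as the rows with about 21 instruments show. All of this stands and limits the claim.

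A reader might also infer that the same GSMR estimates are carried into mtCOJO as evidence of causality. The article says only that earlier results inform those analyses and that MR aids interpretation, and it lists the expected conditioning traits on the basis of previous work.

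It can further be said that an unmeasured confounder could be a heritable common cause, so the caveat is near the mark, and that genomic structural equation modelling elsewhere in Aim 3 models shared factors. Both are fair in part. Neither corrects the printed contrast, which still presents a directional relationship as what distinguishes causality. A promise of best practice does not withdraw a wrong statement.

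The simulations give all SNPs correlated effects, a model in which an outlier filter can do little. Its lack of benefit there should not be generalised.

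**Conclusion.** The point holds as an error in a printed interpretive statement, not as a missing method. That the contrast does not discriminate follows from algebra and needs no assumed input. How often GSMR would reject without causation does depend on assumptions: at r_g 0.2-0.3, about 74-100% for well-powered exposures (about 450 instruments) and about 10-65% with about 21, under the Step 2 inputs. Other inputs move these figures. The second simulation gave 53% and 81% at r_g 0.2 and 0.3 with about 26 instruments, so 10-65% is not an upper bound for sparse instruments in general.

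The consequence is confined to causal wording in secondary post-GWAS analyses under Aims 3 and 4. Ascertainment, the GWAS, heritability and the genetic correlations are unaffected. The correction should be made before results are interpreted.

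**What to change.** Replace the sentence on pleiotropy and causality. State that GSMR tests for correlated SNP effects, that a directional relationship is also expected under correlated pleiotropy, and that causality also gives a non-zero mean effect once alleles are aligned. Give correlated pleiotropy as a reason for caution beside unmeasured confounders.

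Add a summary-statistics method whose null allows genetic correlation without causation, for example a latent causal variable model or a mixture model with a shared factor. Call a result causal only if that method supports it. Otherwise report the GSMR slope as consistent with genetic overlap, including where it is used to interpret mtCOJO.

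The cost is revised wording and one more analysis on the same summary statistics, with no new data. The downside is that fewer results can be called causal, because such methods have less power at 3,000 cases.

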## Background

We describe the Avoidant Restrictive Food Intake Disorder – Genes and Environment (ARFID-GEN) study, which is designed to expand the discovery of genetic and environmental contributions to ARFID risk. ARFID-GEN builds on previous and ongoing genome-wide association studies (GWAS) by the Eating Disorders Working Group of the Psychiatric Genomics Consortium (PGC-ED) as part of a global effort to fully characterize the genetic architecture of all eating disorders (EDs) and explore their relation to each other and to other psychiatric, neurodevelopmental, and metabolic/anthropometric traits.

ARFID-GEN will ascertain, phenotype, and genotype a large sample of children and adults with ARFID. We will apply advanced analytic strategies to test and refine an etiological model of ARFID, explicate heterogeneity, and simultaneously document environmental risk factors for ARFID.

ARFID is associated with high personal and family emotional and financial cost. ARFID, present in 2–5% of the population [1], is marked by the avoidance and/or restriction of food intake resulting in significant weight loss or nutritional deficiency, dependence on feeding supplements, and/or interference with psychosocial functioning. Unlike other EDs, food restriction is not driven by weight and shape concerns, and ARFID may be equally common in males and females [1]. The Diagnostic and Statistical Manual of Mental Health Disorders 5th edition (DSM-5) [2] describes three predominant ARFID presentations that likely overlap [3]: (1) sensory sensitivity (i.e., rejection of food based on sensory qualities such as texture), (2) phobic avoidance of food (i.e., concern about aversive consequences of eating, such as fear of choking), and (3) low interest/appetite. Psychiatric, neurodevelopmental, and somatic medical comorbidities are common, with ~ 50% of ARFID cases having a co-occurring diagnosis [4].

Using existing Swedish twin data, we demonstrated that an ARFID phenotype is highly heritable (twin heritability estimate [h^2^twin] = 0.79; CI:0.71, 0.86), with the remaining variance attributable to nonshared environmental factors [5]. This places ARFID amongst the most heritable psychiatric disorders and on par or higher than anorexia nervosa (AN) (0.50–0.60) [6], bulimia nervosa (BN) (0.50–0.60) [6], and binge-eating disorder (BED) (0.39–0.57) [7, 8]. These results support a GWAS for ARFID.

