#### Aim 4. Genetic relation of ARFID with psychiatric, metabolic/anthropometric, neurodevelopmental, and other relevant phenotypes

To test a conceptualization that ARFID has specific genetic associations with psychiatric, metabolic/anthropometric, and neurodevelopmental phenotypes we will apply: (a) approaches as in Aim 3b, and (b) GSEM to examine genetic, psychiatric, neurodevelopmental, and metabolic/anthropometric factors associated with ARFID. We predict that high sensory sensitivity will be related to autism spectrum disorder (ASD), high levels of phobic avoidance to anxiety and obsessive–compulsive disorder (OCD), and high levels of low interest/appetite to AN. Deliverables: (a) dissection of converging and diverging relations among ARFID and other traits informing and refining its etiology; (b) genetic assessment of ARFID’s relation to other phenotypes, informing nosology.

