#### Case definition (ARFID)

##### Inclusion criteria

Individuals ages 7 + who meet DSM-5 criteria for ARFID. An age 7 + cut-off allows adequate phenotyping with a range of valid instruments available for relevant constructs for this age and older. We anticipate most cases will be pediatric as ARFID typically onsets in childhood. Following a brief online eligibility pre-screen, participants/parents/guardians will be screened for eligibility (for themselves or, in the case of parents/guardians, for their children) and for diagnostic purposes using the questionnaires listed in *Supplement* and Table 1.

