
#### Aim 4. Genetic relation of ARFID with psychiatric, metabolic/anthropometric, neurodevelopmental, and other relevant phenotypes

Analyses will parallel Aim 3 only with an outward focus on traits other than EDs. For r_g_s, we will follow methods applied in the Anorexia Nervosa Genetics Initiative-PGC-ED (ANGI-PGC-ED) Freeze 2 analysis [28], adding additional traits as GWAS summary statistics become available. Only GWAS summary statistics are needed for GSEM, many of which are publicly available. Phenotypes of interest are not directly evaluated in the target sample. Related traits for GSEM may include: lifetime anxiety disorder (ANX), neuroticism, BMI, fat mass, and fat-free mass (available in the UK Biobank); ASD, attention-deficit/hyperactivity disorder (ADHD), post-traumatic stress disorder (PTSD), MDD, and OCD GWAS summary statistics (available from the PGC).

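### Weight loss is one route into the ARFID case group, so genetic correlation, MR and GSEM results with BMI and fat mass can partly reflect the entry criterion, and the planned tools cannot separate the two

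*Protocol article*

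**What the plan says.** The Background of the protocol article defines ARFID by "avoidance and/or restriction of food intake resulting in significant weight loss or nutritional deficiency, dependence on feeding supplements, and/or interference with psychosocial functioning". Entry is open to "Individuals ages 7 + who meet DSM-5 criteria for ARFID" (Inclusion criteria), with no rule on which consequence must be present. Weight loss is therefore one alternative route among four. Controls come from archived genotyped repositories (Specific aims, Aim 1a; Participants, Objective), and no comparable filter is described for them.

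Under Planned data analysis, Aim 3 lists genetic correlations, bidirectional MR, mtCOJO conditioning of the ARFID GWAS on traits that include BMI, and GSEM. On BMI it says: "we expect to detect genetic correlations of BMI with EDs, and MR analyses will aid interpretation of correlation by causality". It also warns against strong causal conclusions from significant MR results, giving possible unmeasured confounders as the reason.

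Aim 4 sets out "To test a conceptualization that ARFID has specific genetic associations with psychiatric, metabolic/anthropometric, and neurodevelopmental phenotypes", and its deliverables include refining the aetiology of ARFID. The traits that may enter its GSEM include "neuroticism, BMI, fat mass, and fat-free mass (available in the UK Biobank").

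The article does not mention overlap between the weight criterion and the body-size traits, and it describes no analysis by criterion route. It refers to a Supplement for detail, which is not at hand.

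**The concern.** Take two people with the same avoidant eating and the same degree of restriction. If the one with genetically lower BMI reaches the weight criterion more easily, that person is more likely to be a case. Cases then differ from controls at BMI variants because of the diagnostic rule, even if avoidant eating shares no genes with BMI.

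MR does not resolve this. Under this mechanism BMI variants do change the probability of being a case, consistently across instruments, so MR would return an effect of lower BMI on case status with no sign of pleiotropy. That is a correct statement about DSM-5 case status. It does not show that BMI biology contributes to avoidant eating. The same ambiguity carries into the genetic correlations and GSEM paths with BMI, fat mass and fat-free mass.

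At stake is the anthropometric part of Aim 4: a result offered as aetiology could arise wholly or partly from the way cases qualify.

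**Working it through.** **No figure to reproduce.** The article gives no genetic correlation, no share of cases by route and no power for this point. What follows shows the possible size under stated assumptions.

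**Inputs from the article.** Cases 3,000 ("Projected: ARFID = 3,000, AN = 50,000, BN = 20,000, BED = 20,000"); ARFID-GEN controls 42,439; prevalence K = 2% to 5% (Background). Effective N = 4/(1/3,000 + 1/42,439) = 11,208.

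**Assumptions not in the article.** Avoidant-eating liability is genetically independent of BMI. SNP heritability is 0.20 to 0.25 for BMI and 0.1 to 0.3 for ARFID. The BMI instrument R² is 5%. The non-weight routes are met with probability p, independently of BMI.

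**Model A: weight route as a hard cut-off, BMI z < -1.** This is the strongest case. P(W) = 0.159, E(BMI|W) = -1.525, E(BMI|not W) = 0.288.

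- Mean case shift m = [P(W)·E(BMI|W) + (1-P(W))·p·E(BMI|not W)] / [P(W) + (1-P(W))·p]
- Weight-only share = P(W)(1-p) / [P(W) + (1-P(W))·p]
- Induced r_g = m·√(h²_BMI/h²_ARFID)/i, where i = φ(t)/K = 2.42 at K = 2% and 2.06 at K = 5%
- MR z = m/√(1/[(11,208/4)·0.05]) = m/0.0845

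For p = 0.35: m = (-0.242 + 0.085)/(0.159 + 0.294) = -0.347. The weight-only share is 0.159·0.65/0.453 = 23%. Induced r_g runs from -0.347·√(0.20/0.30)/2.42 = -0.12 to -0.347·√(0.25/0.10)/2.06 = -0.27. MR z = -0.347/0.0845 = -4.1.

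| p | Weight-only share | Shift (SD) | Induced r_g | MR z |
|---|---|---|---|---|
| 0.8 | 4% | -0.06 | -0.02 to -0.05 | -0.7 |
| 0.5 | 14% | -0.21 | -0.07 to -0.16 | -2.5 |
| 0.35 | 23% | -0.35 | -0.12 to -0.27 | -4.1 |
| 0.2 | 39% | -0.59 | -0.20 to -0.45 | -7.0 |

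**Model B: probabilistic weight route, same prevalence.** The cut-off is replaced by a probit with slope 0, 0.3 or 0.6 on BMI.

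| Weight-only share | Slope 0 | Slope 0.3 | Slope 0.6 |
|---|---|---|---|
| 14% | MR z = 0 | -0.7 | -1.3 |
| 23% | 0 | -1.2 | -2.1 |
| 39% | 0 | -2.0 | -3.6 |

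At 23% and slope 0.3 the shift is -1.18·0.0845 = -0.10 SD. Induced r_g is then -0.10·√(0.20/0.30)/2.42 = -0.03 to -0.10·√(0.25/0.10)/2.06 = -0.08.

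**Model C: simulation of 6 million people.** BMI heritability is 0.25, and 30% of restrictors meet the weight criterion. With no dependence on constitutional BMI, induced r_g is 0.00 even at 41% weight-only. With slopes of 0.5 and 1.0 it is -0.01 to -0.02 at 3% weight-only, -0.05 to -0.14 at 23%, and -0.09 to -0.23 at 41%.

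**Precision of a run without weight-only cases.** Dropping 13.7% (the 14% row) leaves 2,589 cases, and effective N = 4/(1/2,589 + 1/42,439) ≈ 9,760. Dropping 38.8% (the 39% row) leaves 1,836 cases and an effective N of about 7,040.

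**Limit of that run.** If the other routes also depend on BMI (probit slope 0.2), the set without weight-only cases still has a mean shift of -0.16 SD at p = 0.5 and -0.28 SD at p = 0.2.

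**The case against.** The strongest reply is that the criterion is weight loss, not low weight. Loss caused by restriction does not alter germline BMI variants, and if meeting the route is unrelated to constitutional BMI the artefact is exactly nil. This stands. It rules out saying that the results will return the entry criterion, and it means the hard cut-off figures are an upper case.

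A reader might also infer that the plan will present BMI findings as causal. The article does not support that reading: it carries an explicit MR caution and says best practice at the time of analysis will be followed. But the reason given for the caution is unmeasured confounding. Criterion overlap is a different problem, and the caution does not lead to a check for it.

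The plan conditions the ARFID GWAS on BMI and models low weight as a more granular phenotype. Both are partial checks. Conditioning adjusts SNP associations. It does not show whether the component removed was criterion or aetiology, and it leaves the BMI correlation, MR and GSEM estimates as they were.

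It is fair to say that an effect on DSM-5 case status is an effect on the stated phenotype. The difficulty is only in moving from there to aetiology. It is also fair that the quoted sentence concerns eating disorders in general, that the GSEM traits are ones that may be included, and that none of Aim 4's specific predictions concerns BMI. The text directly after the quoted sentence does apply BMI conditioning to the ARFID GWAS.

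Finally, a reader might infer that the full plan has no such sensitivity analysis. That cannot be said without the Supplement. The point rests on what the article states MR will do.

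**Conclusion.** The concern holds as a possibility that the stated interpretation does not allow for. Body-size results can partly reflect how cases qualify, and MR as described cannot distinguish that from BMI-related aetiology of avoidant eating. Two conditions decide the size: how strongly the weight route depends on constitutional BMI, and what share of cases qualify by weight alone. The article gives neither.

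With no dependence the artefact is nil. With about 23% weight-only cases, the simulation and the hard cut-off together give an induced r_g of roughly -0.05 to -0.27, falling to -0.03 to -0.08 at the weakest dependence tried. MR z at that share runs from -1.2 to -4.1. At a 4% share it is negligible even under the hard cut-off. All these sizes rest on assumed heritabilities, instrument strength and independence of the other routes. The point warrants a sensitivity analysis and a limit on wording; it does not show that the planned analyses are invalid.

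**What to change.** Add to Aims 3 and 4:

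- A sensitivity run of every genetic correlation, MR and GSEM analysis that involves BMI, fat mass or fat-free mass. Keep every case who meets at least one of nutritional deficiency, supplement dependence or psychosocial interference, whether or not weight was also lost. Drop only those who qualify by weight alone. Low-weight cases as such should stay in, since removing them would bias the other way.
- A report of the weight-only share, with estimates and intervals from both case sets side by side.
- A statement that body-size results describe DSM-5 case status and are not read as aetiology or causality without regard to this comparison.

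Persistence in the reduced set should not be a pass/fail rule. Loss of an effect may reflect lower power or removal of cases in whom a real effect is concentrated, and persistence may reflect BMI dependence of the other criteria.

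The cost is plan wording and one further GWAS run, with wider intervals: effective N falls from 11,208 to about 9,760 if 14% are dropped, or about 7,040 if 39% are. The route would come from criterion-level answers in the diagnostic questionnaires. The article says only that embedded algorithms determine eligibility, so the sponsor should confirm that the stored answers identify the route.
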